# Antenatal sildenafil administration to prevent pulmonary hypertension in congenital diaphragmatic hernia (SToP-PH): study protocol for a phase I/IIb placenta transfer and safety study

**DOI:** 10.1186/s13063-018-2897-8

**Published:** 2018-09-27

**Keywords:** Sildenafil citrate, Congenital diaphragmatic hernia, Transplacental therapy, Placenta transfer study

## Abstract

**Background:**

Congenital diaphragmatic hernia is an orphan disease with high neonatal mortality and significant morbidity. An important cause for this is pulmonary hypertension, for which no effective postnatal therapy is available to date. An innovative strategy aiming at treating or preventing pulmonary hypertension more effectively is urgently needed. Prenatal sildenafil administration to expectant mothers prevented fetal and neonatal vascular changes leading to pulmonary hypertension in several animal models, and is, therefore, a promising approach. Before transferring this antenatal medical approach to the clinic, more information is needed on transplacental transfer and safety of sildenafil in humans.

**Methods:**

This is a randomized, investigator-blinded, double-armed, parallel-group, phase I/IIb study with as a primary objective to measure the in-vivo transplacental transfer of sildenafil in women in the second and early third trimester of pregnancy (sub-study 1; weeks: 20.0–32.6) and at term (sub-study 2; weeks: 36.6–40). Participants will be randomized to two different sildenafil doses: 25 or 75 mg. In sub-study 1, a single dose of the investigational product will be administered to women undergoing termination of pregnancy, and maternal and fetal blood samples will be collected for determination of sildenafil concentrations. In sub-study 2, sildenafil will be administered three times daily from 3 days before planned delivery until actual delivery, following which maternal and umbilical cord samples will be collected. Proxies of maternal and fetal tolerance as well as markers of fetal pulmonary vasodilation will also be measured.

**Discussion:**

This is the first study evaluating in-vivo transplacental passage of sildenafil in humans.

**Trial registration:**

EU Clinical Trials Register 2016–002619-17, validated on 12 August 2016.

Trial sponsor: UZ Leuven, [name].

**Electronic supplementary material:**

The online version of this article (10.1186/s13063-018-2897-8) contains supplementary material, which is available to authorized users.

## Background

Congenital diaphragmatic hernia (CDH) is a birth defect occurring in 1/2500 newborns and is characterized by a failure of the diaphragm to fully form in early pregnancy. This causes herniation of the abdominal organs into the thorax, which compromises lung development, eventually leading to pulmonary hypoplasia [1]. At birth, the clinical consequence is respiratory insufficiency and persistent pulmonary hypertension (PHT) which cannot simply be solved by surgically repairing the diaphragm. Thanks to advances in postnatal management, survival of neonates with CDH has increased to 70% [2–4]. Despite that, PHT remains a major determinant of mortality and morbidity, with only expert opinions to guide treatment [5, 6].

Today, more than 70% of CDH cases are diagnosed prenatally, following which additional testing is done to estimate the degree of fetal pulmonary hypoplasia and to provide a personalized prognosis [7–11]. The ability to identify a future non-survivor during pregnancy sparks the question for a prenatal intervention to reverse the natural course of the condition. Prenatal lung growth can be stimulated by minimally invasive tracheal occlusion (TO) [12]. The efficacy of this procedure currently undergoes evaluation in a global, open-label randomized clinical trial (https://totaltrial.eu/) [13]. Although TO improves lung size and may thus increase postnatal survival, it only partially improves PHT. Furthermore, TO remains a surgical intervention, with its inherent side effects and complications, such as prematurity, partially offsetting the effect of fetal therapy [14, 15].

As an alternative or complementary treatment to TO, we will investigate the use of transplacentally administered sildenafil. Sildenafil is a selective inhibitor of phosphodiesterase-type-5. It is primarily marketed for the treatment of erectile dysfunction, but also for treating PHT in adults [16]. It enhances nitric oxide (NO)-mediated vasodilation [17], promotes pulmonary angiogenesis and decreases pulmonary arterial remodeling [18, 19]. The drug is effective in children above 1 year of age who have PHT [20]. There is a growing interest in the use of sildenafil for the treatment of PHT of various etiologies in the newborn, including in CDH [21], particularly when other therapies, such as inhaled NO, fail. Such step-up strategy has been recently incorporated in the updated European “Euro-CDH Consortium” consensus neonatal management protocol for CDH infants [22].

Sildenafil has also already been used in pregnant women for maternal PHT or for pregnancy complications such as pre-eclampsia and intrauterine growth restriction [23, 24]. A systematic review summarizing clinical studies on sildenafil use in pregnancy has shown that maternal tolerance and perinatal outcomes are comparable with controls [25]. All this suggests a safe use of sildenafil from mid-gestation onwards.

Given the maternal and fetal safety profile of sildenafil, and given its established use in the postnatal treatment of PHT, the logical next step is to consider sildenafil use *prenatally*. Indeed, this is when the morphologic basis for PHT is being laid down, and, as such, prenatal treatment could potentially prevent PHT.

In two animal models of CDH, sildenafil has been shown to rescue the pulmonary vascular bed [26, 27]. Luong et al. were the first to demonstrate that maternal sildenafil administration reverses the morphologic pulmonary vascular changes associated to CDH in the nitrofen rat model [26]. Given our focus on making fetal interventions for CDH more effective and less invasive, we felt the need to move the concept of sildenafil further along the translational research track. We demonstrated the safety and efficacy of sildenafil in the rabbit [27]. Placebo-exposed CDH fetuses had an increased wall thickness in peripheral pulmonary vessels and significantly less fifth-generation vessels compared to controls. CDH fetuses treated with sildenafil had a medial thickness in peripheral pulmonary vessels in the normal range and a normal percentage of vessels of the fifth generation or higher. Sildenafil also reversed the mean terminal bronchiolar density in CDH fetuses to normal values and improved lung mechanics. Functionally, we could demonstrate reduced in-utero pulmonary vascular resistance by micro-ultrasound Doppler examination. No maternal or fetal adverse effects were observed. In summary, both in the rodent and the rabbit model, antenatal sildenafil administration rescues vascular branching and architecture and improves airway morphometry. These preclinical findings, together with the demonstration of the safety of sildenafil during pregnancy, pave the way for clinical translation.

One last critical step prior to clinical translation is that we need a better knowledge of sildenafil pharmacokinetics and transplacental transfer in vivo. This information is currently not available in the academic literature. This knowledge gap is explained by the fact that the product is currently used for maternal indications or to improve the flow in the uterus and placenta [24, 28, 29]. In these conditions fetal effects are less relevant, hence they were less studied and fetal drug levels were not measured. We have recently performed ex-vivo placental transfer studies [30]. We demonstrated that sildenafil crosses the placenta ex vivo at a rate that is independent from the initial maternal concentration and that there is sufficient placental transfer to reach therapeutic fetal drug levels at non-toxic maternal concentrations. These results need now to be validated in vivo.

## Methods and trial design

### Objectives

The main objective of the study is to evaluate the transfer of sildenafil through the second and third trimester human placenta in vivo.

Secondary objectives are:To evaluate maternal, fetal and neonatal toleranceTo evaluate the effect of sildenafil on the fetal pulmonary circulation

### Trial design

This is a randomized, investigator-blinded, double-armed, parallel-group, phase I/IIb study consisting of two different sub-studies recruiting simultaneously:Second trimester placental transfer study (sub-study 1)The primary outcome of this sub-study is the fetal plasma sildenafil level after oral administration maternally. Fetal plasma will be obtained by fetal cardiocentesis or cordocentesis, required for administration of the drugs used for feticide at the time of pregnancy termination [31, 32]. Maternal blood sampling will be performed simultaneously via peripheral venous puncture.Secondary endpoints are:Doppler ultrasound measures of pulmonary vasodilatation: change in the acceleration time/ejection time (AT/ET) ratio of the main fetal pulmonary artery and of the pulmonary artery branch closest to the ultrasound probe between baseline and the time of fetal blood sampling. Additional measures of blood flow resistance in the fetal main pulmonary artery and in the right and left pulmonary artery branch (Pulsatility Index, Resistance Index, peak systolic velocity, peak early diastolic reversed flow) will also be collectedEffect of sildenafil on the fetal systemic circulation: change in the Doppler waveform of the umbilical artery, between baseline and blood samplingSimulated maternal and fetal pharmacokinetic profilesMaternal tolerance, measured as change in blood pressure, heart rate and oxygen saturation compared to baseline, and incidence of side effects, including any kind of visual disturbanceThird trimester placental transfer and safety study (sub-study 2)The primary endpoint is sildenafil transfer at term, expressed as a ratio of the neonatal over the maternal sildenafil plasma concentration. Neonatal venous blood samples will be collected from the umbilical cord at delivery. Maternal blood sampling will be performed via peripheral venous puncture.Secondary endpoints are:Doppler ultrasound measures of pulmonary vasodilatation as described aboveEffect of sildenafil on the fetal systemic circulation: change from baseline in the Doppler waveform of the umbilical artery, mean cerebral artery, ductus venosus, change in fetal heart rate monitoring patternEffect of sildenafil on the maternal placental circulation: change from baseline in the Doppler waveform of the uterine arteriesSimulated maternal and fetal pharmacokinetic profilesMaternal tolerance measured as change in blood pressure, heart rate and oxygen saturation compared to baseline, and incidence of side effects, including any kind of visual disturbanceNeonatal tolerance, measured as trend in mean arterial blood pressure during the first 24 h of life, vasoactive inotropic score [33] at 24 h of life and early (< 24 h) lung function, expressed as Oxygenation Index and alveolar-arterial oxygen gradient

For both sub-studies, participants will be randomized to one of two parallel groups receiving different doses of sildenafil (sildenafil 25 or 75 mg). No placebo control is foreseen. The protocol follows the Standard Protocol Items: Recommendations for Interventional Trials (SPIRIT) recommendations for interventional trials (Additional file 1). 

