### Interventions

In both sub-studies, sildenafil tablets will be administered orally to the mother as this administration route is the most practical and clinically most acceptable for sustained administration, especially in pregnant women. The half-life of sildenafil after oral administration is about 4 h [34]. Therefore, the most commonly used administration schemes for chronical conditions even in pregnancy consist in three administrations daily [20, 35–37].

Two sildenafil doses have been selected according to previously published literature and to our ex-vivo data on placental transfer [30], i.e., 25 and 75 mg. A dose of 25 mg three times daily has been proven safe in the treatment of pregnancies complicated by intrauterine growth retardation (IUGR) [24]. A dose of 75 mg three times daily is the maximum dose used in a trial on pregnant women affected by pre-eclampsia, without any fetal or maternal side effects being reported under that dose [23].

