#### Third trimester placental transfer and safety study (sub-study 2)

Participants will be randomly assigned to one of two study groups: dose 1 (25 mg three times daily) and dose 2 (75 mg three times daily)Baseline visit: the study procedures will involve measurements of maternal blood pressure, heart rate and oxygen saturation; fetal ultrasound for assessment of fetal wellbeing and Doppler examination of the fetal main pulmonary artery and contralateral pulmonary artery branch, mean cerebral artery, umbilical artery, ductus venosus; Doppler examination of the uterine arteries; fetal heart rate monitoring (cardiotocography)During sildenafil administration (from day 0 until occurrence of labor, specifically at 2 and 50 h after the first administration) the study procedures will be the same as in the baseline visit. Treatment compliance and any side effect will also be reported. One maternal blood sample will be collected on day 2 (50 h after the first administration) for determination of maternal plasma sildenafil concentrationDuring labor and at delivery fetal heart rate, maternal blood pressure, heart rate and oxygen saturation, and eventual side effects will be recorded as part of the clinical protocol. At the moment of delivery, one maternal and one umbilical cord blood sample will be collected for determination of sildenafil concentrationAt the neonatal follow-up visit (day 1 after birth), mean arterial blood pressure, vasoactive inotropic score [33] and early (< 24 h) lung function, expressed as Oxygenation Index and alveolar-arterial oxygen gradient will be recorded. Adverse effects, if any, will be recorded

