#### Third trimester placental transfer and safety study (sub-study 2)

To obtain reliable pharmacokinetic data, we plan to include six patients for each tested dose (total = 12 patients). For the reasons given above in sub-study 1, block randomization (block size = 4) will be used.

We expect a 50% incidence of maternal or fetal (i.e., not isolated cases, fetuses having had fetal therapy) conditions representing an exclusion criterion for the study and a 50% rejection rate. Speculating that the drop-out rate after inclusion will be less than 10%, we will need to assess for eligibility a total of 52 women with ongoing pregnancies and CDH at term.

The Data Safety and Monitoring Committee will evaluate drop-out rate ad interim, and is authorized to adjust sample size, if appropriate.

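### Sub-study 2 scores vasoactive support only at 24 h of life, so early weaned support is missed, and its neonatal tolerance data cannot separate drug exposure from CDH severity

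*Protocol article*

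**What the plan says.** The Trial design section lists neonatal tolerance as a secondary endpoint of sub-study 2. Its components are the mean arterial pressure trend over the first day and "vasoactive inotropic score [33] at 24 h of life and early (< 24 h) lung function", with lung function given by the Oxygenation Index and the alveolar-arterial gradient. The list of sub-study 2 procedures places these recordings at the day 1 neonatal visit and adds that adverse effects are recorded.

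The inclusion criteria for sub-study 2 accept isolated CDH on either side and of any severity of hypoplasia. The Background section describes what the hernia itself does: "At birth, the clinical consequence is respiratory insufficiency and persistent pulmonary hypertension (PHT". It also says that in prenatally diagnosed cases "additional testing is done to estimate the degree of fetal pulmonary hypoplasia and to provide a personalized prognosis", so a severity measure should usually be available before birth.

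On comparison, the Trial design section states "No placebo control is foreseen". The two doses are randomised with six women each, and in the sample size section "block randomization (block size = 4) will be used", with no severity stratum mentioned. The section headed Statistical analysis plan summarises data by sub-study and dose group and defines baseline as the last value before the subject's first dose. The covariates it names alongside the pharmacokinetic model are gestational age and maternal height and weight. Its adverse-event paragraph closes by calling the analysis descriptive, without inferential testing.

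**The concern.** There are two separate weaknesses.

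The first is the timing of one endpoint. A score taken once at 24 h records the support running at that moment. Support needed in the first hours and then withdrawn leaves no trace in it. The pressure trend does not repair this, because pressure kept normal by vasoactive drugs looks the same as pressure that needed no help.

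The second is interpretation. Oxygenation Index and alveolar-arterial gradient are abnormal in CDH without any drug. Every newborn in the sub-study is exposed to sildenafil, and none can have a value from before the mother's first dose. A poor set of values therefore cannot be assigned to the drug, and a good set cannot clear it.

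At stake is what the sub-study, which carries safety in its title, can say about newborns. The Discussion section expects it to supply first tolerance data and safety information for other uses of sildenafil in pregnancy.

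**Working it through.** **The plan's own figure.** The plan gives no calculation for neonatal tolerance. The only calculated figure for sub-study 2 is 52 women to be assessed. It is reproduced by 13/(0.5 × 0.5) = 52, where including 13 to keep 12 implies drop-out of 1 − 12/13 = 7.7%, in line with the stated value below 10%. Six per arm is therefore the basis for what follows.

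**What a single score at 24 h records.** Assumption: the score reflects support running at the time it is taken (its source is cited but not shown).

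| Newborn | Score at 24 h | Highest score, first 24 h |
|---|---|---|
| No support | 0 | 0 |
| Support started and weaned before 24 h | 0 | > 0 |
| Support still running at 24 h | > 0 | > 0 |

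The endpoint as fixed cannot distinguish the first two rows.

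**Drug remaining at 24 h.** Transfer stops at birth, so the fraction left is 2^(−24/t½). The Interventions section gives one value: "The half-life of sildenafil after oral administration is about 4 h". With 4 h, 2^(−6) = 1.6%. No newborn half-life is given; assumed values of 8, 12 and 24 h give 12.5%, 25% and 50%. The range is wide, but in every case transferred drug is higher in the first hours than at 24 h. The table above does not depend on any half-life.

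**Which comparisons exist.**
- Drug versus no drug: none, because there is no unexposed group.
- Change within a newborn: none, because baseline precedes the first maternal dose.
- 75 v 25 mg: randomised, six per arm.

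**Precision of the dose contrast.** The 95% half-width is t(0.975, 10 df) × √(2/6) = 2.228 × 0.577 = 1.29 SD. At an assumed two-sided 5% level and 80% power, the detectable difference is (1.96 + 0.84) × 0.577 = 1.62 SD by the normal approximation and 1.80 SD by the t distribution. Power for a 1 SD difference is 35% by the t distribution.

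**Chance imbalance in severity.** The number of severe cases is not given. Assume 4 or 6 of 12, allocated 6:6, with C(12,6) = 924.
- 4 severe: P(2:2) = 6 × 70/924 = 420/924 = 0.455, so P(3:1 or worse) = 0.545. P(4:0) = 2 × 28/924 = 0.061.
- 6 severe: P(3:3) = 20 × 20/924 = 400/924 = 0.433, so P(4:2 or worse) = 0.567. P(5:1 or worse) = 2 × (36 + 1)/924 = 0.080.

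Simulating three blocks of four gives 0.545 and 0.566 for any imbalance, and 0.062 and 0.079 for marked imbalance. The blocks balance numbers, not severity.

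**How much severity could move the contrast.** If severity explains a share R² of a marker's variance, the chance difference it produces between arms has SD √R² × √(2/6). For R² from 0.25 to 0.75 (assumption) this is 0.29 to 0.50 SD.

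**The case against.** Several objections carry weight.

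- **Dose is randomised.** Severity adds noise to the 75 v 25 mg contrast, not bias. A reader might infer that drug and severity cannot be told apart even between doses, or that the figures mostly measure how bad the hernias were. The documents do not support that: they give no variance share, and the probabilities near 0.55 count any departure from an even split. Marked imbalance is unlikely. The sample size section also counts previous fetal therapy among the excluding conditions, which may narrow the severe end.
- **Dose selection does not rest on these markers.** A reader might infer that a misleading tolerance result would set the phase III dose. The Statistical analysis plan section predicts dose from measured concentrations through the pharmacokinetic model, and no rule ties neonatal tolerance to it.
- **The first hours are not wholly unobserved.** The pressure trend, lung function before 24 h and recorded adverse effects all cover them. This stands, but none of these scores the vasoactive support itself.
- **A condensed article may leave listings and covariates to the full plan.** That is fair for the individual displays. It does not cover the 24 h time point, which the article fixes as part of the endpoint.
- **CDH as the driver of blood pressure and inotropic need** is supported only indirectly, by the mention of right-sided heart failure in the Discussion section. The direct support is for the respiratory markers.
- **A peak score may follow disease severity more closely than a 24 h score.** This is plausible, and is a reason to keep both and show them beside lung size.

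**Conclusion.** The point holds as a minor to moderate one on a secondary endpoint. The single score at 24 h misses support given and weaned earlier; this follows from the definition, on the assumption that the score reflects current support.

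Separately, sub-study 2 cannot distinguish drug from no drug in these newborns, because there is no unexposed group, no neonatal baseline and unrestricted severity. The dose contrast is sound in expectation but wide (±1.29 SD). Some severity imbalance is more likely than not, and marked imbalance has a probability of about 6% to 8%, if 4 or 6 of 12 are severe.

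The primary transfer ratio is untouched. The half-life figures illustrate the timing and do not show that the drug is gone by 24 h, since no newborn value is given.

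**What to change.** 1. Report the highest vasoactive inotropic score in the first 24 h alongside the value at 24 h, taken from the same first-day record as the blood pressure trend.
2. Show each newborn's tolerance results individually against the prenatal lung-size estimate, the side of the hernia and the measured cord sildenafil level. Treat any adjusted dose comparison as exploratory only, since adjustment in 6 v 6 is unstable.
3. State that neonatal results are descriptive by dose and can neither establish nor exclude a drug effect. Do not make the reporting of a possible safety signal depend on its surviving adjustment, because that could discount a real one.

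The cost is a little chart abstraction and a less clean-cut tolerance statement. No patients, visits or arms are added. The changes do not supply an unexposed comparator, so the drug versus no drug question stays open and item 3 says so.

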### Study population

#### Second trimester placental transfer study (sub-study 1)

##### Inclusion criteria

Volunteer with singleton pregnancy undergoing second trimester or early third trimester termination of pregnancy for fetal anomalies not interfering with normal lung developmentMaternal age > 18 and < 45 years (to allow consent and avoid age-related cardiac risks, respectively)

